3. The stepped wedge design has been used for scientific reasons such as to allow detection of underlying trends or control for time effects (Brown and Lilford, 2006, Mdege et al., 2011); this is of interest in the current study, as the multiple time points of data collection will allow for investigation of time effects to answer relevant questions– for example, does the effect dissipate over time, or does the intervention require time to consolidate and therefore have impact on patient outcomes.
4. Another advantage of the stepped wedge design over a parallel CRCT is that it requires fewer clusters (Hussey & Hughes, 2007), and it maximises power as the intervention effect is estimated on both between-cluster and within-cluster comparisons (Mdege et al, 2011; Pearson et al, 2010).

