## Sample size

The primary outcome measure, the PSFS, shows that for any individual patient, the minimal detectable change (90%CI) for an aggregate of 3 or more activities is 2 points; the minimum detectable change (90%CI) for a single activity is 3 points. In this study, we are looking for a mean difference of 1 point greater improvement in PSFS scores of patients whose physiotherapists who have received the intervention compared with the PSFS scores of patients whose physiotherapists have not yet received the training, as well as a greater proportion of patients achieving the level of minimal detectable difference. The following data values were used for the power calculation: mean changes on the PSFS from usual training to the new training of 1 point, and a Standard Deviation within each group of 2. The standard deviation was on the basis of PSFS data collected from an audit of 191 patients who had received treatment at the University Health

Board physiotherapy department, which is a slightly more conservative estimate than standard deviation values of PSFS outcomes from published studies (Hefford et al., 2009, Young et al., 2010, Costa et al., 2009).

A paper published on the design and analysis of stepped wedge designs (Hussey and Hughes, 2007) investigated the statistical characteristics of the stepped wedge design for CRCTs, and through the use of theoretical calculations and simulation the authors outline a procedure for computing power in stepped wedge trials. Using this procedure, a power calculation was carried out by [name], Senior Lecturer in Statistics, Swansea University in discussion with the rest of the research team. The power calculation is summarised below:

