### **Power calculation: summary**

Following the notation of Hussey & Hughes (Hussey and Hughes, 2007), and defining

- I to be the number of physios (the maximum available would be 18; assuming recruitment of two-thirds of the maximum to be a realistic prospect, so we are primarily interested in  $I = 12$ )
- T to be the number of time points (4 time points are required to allow baseline measures and for 3 clusters to cross over from control to intervention, so we are primarily interested in  $T = 4$ )
- N to be the number of observations per physiotherapist per time point.

The model is

$$Y_{ijk} = \mu + \alpha_i + \beta_j + \theta X_{ij} + \varepsilon_{ijk}$$

where  $Y_{ijk}$  is the  $k^{th}$  observation at time  $j$  for physiotherapist  $i$ , and we assume that there is a random physiotherapist effect, so

$$\alpha_i \sim N(0, \tau^2)$$

and some random variation across observations, so

$$\varepsilon_{ijk} \sim N(0, \sigma_\varepsilon^2)$$

with independence everywhere. The  $X_{ij}$  are indicator variates, with value 0 before the intervention, and the value 1 thereafter. The range of indices are  $i = 1, \dots, I; j = 1, \dots, T$  and  $k = 1, \dots, N$ . We take  $\beta_T = 0$  in order to avoid identifiability problems, and wish to consider  $\vartheta$ , the difference in means in the control and intervention group. The variance of  $\hat{\vartheta}$  is given in equation (8) in Hussey & Hughes (Hussey and Hughes, 2007), and its calculation requires the specification of  $\sigma_\varepsilon^2$  and  $\tau^2$ , with  $N$  appearing through

$$\sigma^2 = \frac{\sigma_\varepsilon^2}{N}$$

Omitting some algebra, statistical power, based on the usual 95% confidence level, is defined by

$$1 + \Phi(-1.96 - \Delta) - \Phi(1.96 - \Delta)$$

where

$$\Delta = \frac{\theta_A}{\text{Var } \hat{\theta}}$$

and  $\Phi(\bullet)$  is the usual cumulative distribution function for the standard Normal distribution, and is implemented in EXCEL as =NORMSDISTO.

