Another challenge is the possibility that the full effect of the intervention may not be realized until several time intervals following implementation, for example, the intervention being 50% effective after the first time interval, 75% effective after the second time interval and 100% effective after the third time interval (Hussey and Hughes, 2007). Delayed effects from the intensive mentoring for clinical reasoning facilitation are possible, with physiotherapists requiring time to consolidate and make practice changes. The overall effect of these delayed effects would be to reduce power. Such delays can be modelled into the power calculations, and power can be recovered in part by adding additional measurement periods to the end of the trial. However, it is preferable to address this issue by making the time intervals sufficiently long to see the effects of the intervention realized in a single interval (Hughes, 2007, Hussey and Hughes, 2007). To address this, the clinicians who will act as clinical mentors in this study were asked to reflect on their own experience following mentoring programmes from their Masters courses, and estimate what time period they thought would be sufficient to consolidate knowledge and change practice. All responses estimated between 6-12 months. To this end, each time period will be 12 months long, with the intervention delivered at the beginning of the time period and the data collection at the end of the period to allow for the full effects of the intervention to make an impact.

One group of authors (Brown et al., 2008) highlight the amount of data collection required as the main disadvantage of the stepped wedge design, which could make the cost of using the design prohibitive, unless

the study can use routine, or other easily collected data. This study aims to collect patient outcome data at first and final appointments which is part of routine practice in the physiotherapy service at the Cardiff and Vale University Health Board. An additional collection of these outcomes will take place 12 months post discharge by telephone. Demographic and cost-effectiveness data will be collected at the same time in a single compiled questionnaire. This would certainly fit the description of routine, easily collected data.

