## **Conclusions and applications**

To conclude the discussion of all of these issues, the selection of the stepped-wedge design would appear to be the most appropriate to address the research problem and research questions. The alternatives of parallel designs (crossover or non-crossover) would be limited by issues relating to balancing covariates, sample size, logistics of intervention delivery and potential contamination. The arguments presented for the advantages of crossover methodology used elsewhere in healthcare education are compelling, and the use of stepped-wedge designs in evaluating educational interventions reinforce these arguments. By employing a longitudinal study design, improvements are expected to be made over time as skills are learned, applied and refined; the stepped-wedge design allows for the investigation of time as a variable in the final analysis. The timings of data collection are important; early implementation of the intervention within the time period, data collection near the end of the time period, and sufficiently long time periods to allow for delays in effects from the intensive mentoring for clinical reasoning facilitation, due to time required to consolidate and make practice changes. The use of usual training as control is also appropriate; a non intervention control in this instance would be ethically unacceptable – withdrawing training for staff responsible for patient care - as well as unhelpful for cost-effectiveness analysis where comparison should be made as closely as possible with usual practice (Gray et al., 2010). The assessment issue of recognized assessment tools pre- and post-exposure raised by Murray and colleagues (Murray et al., 1997a) is also addressed.

The overall structure of the quantitative component of the project is outlined and summarized in the consort diagram in figure 5.

Figure 5: CONSORT 2010 Flow Diagram of Quantitative Component of Trial

[figure not shown]

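### The single 0/1 intervention term gives the third-year effect a negative weight, so a steady fade or late build-up would put the estimate outside the true yearly effects, and no time-since-mentoring analysis is specified

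*Protocol*

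**What the plan says.** Under Power calculation: summary, the protocol writes one model: a mean, a random physiotherapist intercept, a fixed effect for each period, and one intervention effect multiplied by "indicator variates, with value 0 before the intervention, and the value 1 thereafter". Statistical methods bases the analysis on the same stepped-wedge methods paper, and describes observations falling into two groups plus a random intercept. The section on challenges adds that time effects will be in the model; these are calendar-period terms. No section writes a term for time since mentoring.

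The protocol nevertheless treats change over time as a question of interest. The third of its four reasons for the design (listed after Figure 2) is to find out "does the effect dissipate over time, or does the intervention require time to consolidate and therefore have impact on patient outcomes". Conclusions and applications repeats that "the stepped-wedge design allows for the investigation of time as a variable in the final analysis".

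The challenges section mentions a gradual effect, for example "50% effective after the first time interval, 75% effective after the second time interval and 100% effective after the third time interval". It names loss of power as the consequence. Its answer is that "each time period will be 12 months long", chosen because the mentors estimated 6 to 12 months to consolidate.

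**The concern.** Three sequences cross over at periods 2, 3 and 4, so the first sequence is measured in its first, second and third year after mentoring, the second sequence in two of those years and the third in one. With one 0/1 term, all these cells share a single effect. If the true effect changes with time since mentoring, the estimate is a weighted sum of the yearly effects with weights set by the design. Nothing guarantees that the weights are positive.

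Two things are at stake. The headline number could be read as the average effect of mentoring when it is not one. And the written analysis does not address the consolidation or dissipation question that helped justify the design.

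**Working it through.** **Inputs.** Power calculation: summary gives I = 12 physiotherapists ("assuming recruitment of two-thirds of the maximum to be a realistic prospect") and T = 4 ("4 time points are required to allow baseline measures and for 3 clusters to cross over from control to intervention"). I take four physiotherapists per sequence, which matches the U, W and V printed in Appendix E. Base case details gives N = 9, tau = 1 and an effect of 1 point. Sample size gives "a Standard Deviation within each group of 2". So the variance of a cell mean is 4/9 = 0.4444, and the ICC is 1/(4 + 1) = 0.2.

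**Step 1: reproduce the protocol's figure.** Let s2 = 0.4444 and t2 = 1. From the layout:

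- U = 4 × (3 + 2 + 1) = 24
- W = 0 + 4² + 8² + 12² = 224
- V = 4 × (9 + 4 + 1) = 56

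Var = I·s2·(s2 + T·t2) / [(I·U − W)·s2 + (U² + I·T·U − T·W − I·V)·t2]

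= 5.3333 × 4.4444 / [64 × 0.4444 + (576 + 1152 − 896 − 672) × 1]

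= 23.7037 / (28.4444 + 160) = 0.125786

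The SE is 0.3547, 1/SE = 2.8196 and the power is 0.805, as in Base case details and Appendix E. (The text prints the standardised effect as effect over variance. The spreadsheet divides by the SD, which is correct.)

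**Step 2: weights by year since crossover.** The generalised least squares estimator with this variance is a linear combination of the cell means. Its coefficients, summed over the four physiotherapists in each sequence, are:

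| Sequence | Period 1 | Period 2 | Period 3 | Period 4 |
|---|---|---|---|---|
| Crosses at 2 | -0.255 | +0.500 | +0.123 | -0.255 |
| Crosses at 3 | 0 | -0.377 | +0.377 | 0 |
| Crosses at 4 | +0.255 | -0.123 | -0.500 | +0.255 |

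- Year 1: 0.500 + 0.377 + 0.255 = 1.132
- Year 2: 0.123 + 0 = 0.123
- Year 3: -0.255

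The weights sum to 1. The only third-year cell is the first sequence in period 4. By then every sequence is mentored, so that cell mainly helps to estimate the period effect.

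**Step 3: expected estimates.**

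- Constant 1, 1, 1: 1.00, no bias.
- Fade 1.0, 0.75, 0.5: 1.132 + 0.092 − 0.127 = 1.10, above the largest true effect.
- Build-up 0.5, 0.75, 1.0: 0.566 + 0.092 − 0.255 = 0.40, below the smallest true effect.

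Against the year-1 effect the bias is about 0.097 in each case, or 0.097/0.355 = 0.27 of an SE.

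**Step 4: dependence on the ICC (N = 9).** The Appendix E row labelled tau matches the printed ICCs and powers only if read as tau squared; the base case is the same either way.

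| ICC | Year 1 | Year 2 | Year 3 | Build-up gives | Fade gives |
|---|---|---|---|---|---|
| 0 | 0.750 | 0.250 | 0 | 0.56 | 0.94 |
| 0.05 | 0.999 | 0.167 | -0.166 | 0.46 | 1.04 |
| 0.10 | 1.071 | 0.143 | -0.214 | 0.43 | 1.07 |
| 0.20 | 1.132 | 0.123 | -0.255 | 0.40 | 1.10 |
| 0.33 | 1.163 | 0.112 | -0.276 | 0.39 | 1.11 |
| 0.50 | 1.181 | 0.106 | -0.287 | 0.38 | 1.12 |

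A linear change leaves the range once the ICC exceeds about 0.022. Every monotone change does so once the year-1 weight exceeds 1, at an ICC of about 0.053.

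**Step 5: models with time since crossover (base case, same 432 observations).**

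- Separate yearly effects: SE 0.377 (year 1), 0.544 (year 2) and 0.785 (year 3).
- Linear term in years since crossover: SE 0.370 for year 1 and 0.274 for the slope. Power for a slope of 0.25 points per year is about 0.15. The year-1 estimate has weights 0.885, 0.229 and -0.115, so it is unbiased only if the change is linear.

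**The case against.** The 0/1 coding is quoted from the power section, where a constant-effect model is usual, and the exact form of a time-since-intervention term is often left to a statistical analysis plan. That is fair in part. But Statistical methods carries the same approach and a two-group description into the analysis, and the time effects it adds are calendar periods. A plan that followed the protocol would inherit the coding.

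A reader might infer several stronger points that the documents do not support:

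- **That the trial cannot answer its own question.** The design collects data in the first, second and third year after crossover, so an analysis by exposure time is possible. It is only unspecified, and it will be imprecise.
- **That the protocol predicts a 50/75/100% build-up.** The pattern is a generic example, and the 12-month periods were chosen so that the full effect appears within one interval. Build-up beyond a year is thus less likely by design. That step does nothing about fading.
- **That the coding cuts power from 0.805 to 0.21 under that pattern.** The power there is 0.21, but an unbiased estimate of a 0.5-point year-1 effect with the same SE would have only 0.29. Most of the loss comes from halving the effect.
- **That any change over time pushes the estimate out of range.** An effect that rises and then falls may leave it inside. At ICC 0 the year-3 weight is zero. If period effects were dropped, which Statistical methods allows when no temporal effect is found, the weights would be 0.6, 0.3 and 0.1.

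Nor does a linear exposure term estimate the year-1 effect more accurately. Under the linear examples its mean squared error is 0.370² = 0.137, against 0.126 + 0.097² = 0.135 for the constant-effect model.

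**Conclusion.** The point holds in conditional form. With period effects and the base-case values, the constant-effect estimate is not an average of the yearly effects: the third year enters at -0.255. A steady fade, or a build-up that continues past the 12-month step, therefore gives an expected estimate outside the range of the true yearly effects (1.10 and 0.40 in the examples). This rests on monotone change, on period effects being kept, and on an ICC above about 0.05 at N = 9 (about 0.02 suffices for linear change). If the effect is constant from the first measurement on, there is no bias.

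The practical size is moderate. As an estimate of the first-year effect, the result is off by about 0.1 point in these examples. As a statement about the average or lasting effect it can mislead more: the mean true effect in both examples is 0.75, so the error is about 0.35 point. The gap between the stated question on consolidation and the written model is real, and the data already planned can address it.

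**What to change.** Keep the constant-effect model, but state that it mainly reflects the first-year effect, and give its weights by year since crossover (at the base case +1.132, +0.123, -0.255; recalculated at the estimated ICC and achieved numbers).

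Prespecify a supporting analysis on the same data with fixed period effects, the random physiotherapist intercept and time since crossover. Use either separate yearly effects, which assume no shape, or a linear term. Report it as the answer to whether the effect dissipates or consolidates.

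The cost is a little more analysis, with no extra patients, visits or design change. The price to state openly is low precision for change over time: about 0.15 power for 0.25 points per year, and about 0.77 points per year needed for 80% power (2.8 × 0.274). A non-significant slope must not be read as evidence of a stable effect. Making an exposure-time estimate the primary analysis instead is a choice, not a requirement; with the linear term, power for a 1-point year-1 effect would be about 0.77 rather than 0.805.

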#### Base case details

- Here, we take  $\theta = 1$  (that is, assume that the average effect of the intervention is 1), and (based on calculations on previous data) set  $\sigma_\varepsilon = 2$ . The remaining calculations are laid out in the attached spreadsheet, where, for illustration, if we take  $N = 9, \tau = 1$  then

$$Var(\hat{\theta}) = 0.12576 \dots,$$

and

$$\Delta = 2.819574$$

so that the power is

$$1 + \Phi(-1.96 - 2.8196) - \Phi(-1.96 - 2.8196) \simeq 1 - \Phi(0.8596) \simeq 0.805$$

- This implies that, in order to achieve a power of 0.8, we need a total of  $4 \times 12 \times 9 = 432$  observations.

#### Other cases

It should be strongly emphasized that the power calculations are sensitive (in varying degrees) to changes in  $\theta, \sigma_\varepsilon$  and  $\tau$ . The spreadsheet in appendix E summarizes the power for other combinations of  $\tau, N$ , and these are displayed in the graph in the spreadsheet as a function of  $N$  for the same  $\theta, \sigma_\varepsilon$ . The chosen values of  $\tau$  may also be summarized via the intra-class correlation

$$p = \frac{\tau^2}{\sigma_\varepsilon^2 + \tau^2}$$

For most cases of  $\tau$  yielding  $p$  in the range  $[0, 0.5]$ , the required power of 0.8 is achieved with between 6 and 10 observations per physiotherapist per time point.

#### Randomisation

The stepped wedge design is a one-way crossover design in which different clusters cross over (switch treatments) at different time points (Mdege et al., 2011). In addition, the clusters cross over in one direction only—typically, from control to intervention. The first time point usually corresponds to a baseline measurement where none of the clusters receive the intervention of interest. At subsequent time points, clusters initiate the intervention of interest and the response to the intervention is measured. More than one cluster may start the intervention at a time point, but the time at which a cluster begins the intervention is randomized (Brown and Lilford, 2006, Hussey and Hughes, 2007).

Enrollment: participating physiotherapists will be recruited by the lead researcher by invitation on the basis of inclusion criteria. They will be approached by the lead researcher, and issued with participant information sheet version 2.0 (see appendix C). The lead researcher will also obtain written consent with participant consent form version 2.0 (see appendix C). During data collection periods, patients will be recruited by their physiotherapist, and issued with patient information sheet version 1.0 (see appendix B). The physiotherapist will also obtain written consent with patient consent form version 1.0 (see appendix B).

Sequence generation: once consented by the lead researcher, participating therapists will be directed to the clinical mentors. The clinical mentors will then randomly allocate the clusters of physiotherapists (clustering by site) to the sequence of intervention (to receive the intervention in time period 2, 3 or 4), by computer programme (Randomization.com, 2008).

Allocation concealment: The sequence generation will be performed by the allocated mentor, in order to ensure that this sequence allocation will be adequately concealed from the lead researcher, who will remain blinded to the sequence until after the data collection and analysis period is completed. These measures for blinding, sequence generation and allocation concealment are implemented to reduce the risk of bias, as highlighted by the Cochrane risk of bias tool (Armijo-Olivo et al., 2010, Lundh and Gotzsche, 2008).

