## Methods - Interventions

### Intervention

The first step (time point) corresponds to a baseline measurement where none of the clusters receive the intervention, which is usual practice for this design (Hussey and Hughes, 2007). At each subsequent step a cluster of participating physiotherapists (a department of the MSK outpatient physiotherapy service) will cross over from control to receive the intervention - a 150 hour clinical mentorship programme, aimed at facilitating clinical reasoning. This will be delivered to participating physiotherapists by mentors who are MACP members, having qualified at MSc / PgD level from a higher education establishment, and who have experience in delivering this form of mentorship at post-graduate level. The intervention will be delivered at the start of the time period, to allow for consolidation and application of the programme, before data collection occurs at the end of the time period. This intervention is selected on the basis that the use of mentorship in the context of clinical placement is established practice in Master's programmes seeking to develop expert practice and has strong support from qualitative literature as outlined earlier. The intervention will take place in the usual clinical context of the participating physiotherapists (as is current practice), consisting of the mentors observing the participating physiotherapists assessing and treating new and follow-up patients, discussing and facilitating clinical reasoning processes immediately after the patients have left. While this programme needs to be fluid enough to address identified learning needs and errors in clinical reasoning, a framework on which to hang discussion, feedback and reflection sessions will help to standardize the intervention to a point; the dialectical clinical reasoning model of Jones and Edwards, 2007 (see figure 4 below) will be implemented to this end. This model has been selected due to its flexibility for management and assessment paradigms, its adaptability to patient situations and presentations, and its underpinning research (Edwards et al., 2004, Edwards et al., 2006, Edwards and Jones, 2007). Failure of participants to receive the intervention will be reported, as well as the reasons for such failure.

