### **Blinding (Masking)**

As with all other evaluations, masking patients, caregivers and observers, as well as those undertaking the statistical analysis is important in minimising information bias (Schulz et al., 2002, Schulz and Grimes, 2002). Due to the fact that in stepped wedge trials the timing of intervention rollout is the unit of randomization, the participating physiotherapists and intervention implementers (clinical mentors) are aware of which cluster is receiving the intervention (Brown et al., 2008, Mdege et al., 2011). However, it is possible to blind the outcome assessors, in this case the lead researcher (who will be unaware of the sequence allocation when analysing outcome data) and the independent observer of physiotherapist performance. This blinding of outcome assessors and use of sequence generation and allocation concealment is essential to enhance internal validity (Brown et al., 2008). Patients submitting their outcomes will also be unaware of whether or not their allocated physiotherapist has received his/her intervention.

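### Nothing withholds the crossover order from the therapists who recruit patients and help score the primary outcome, so they may know their own crossover date while still collecting control data

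*Protocol*

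**What the plan says.** Under *Randomisation* (sequence generation), therapists consent, are sent to the clinical mentors, and "The clinical mentors will then randomly allocate the clusters of physiotherapists (clustering by site) to the sequence of intervention", that is, to period 2, 3 or 4. This is a single draw of the full order. The paragraph on allocation concealment names one person from whom it is hidden, the lead researcher. *Blinding (Masking)* adds the independent observer of therapist performance, and says patients will not know their therapist's status. Of the therapists it says that "the participating physiotherapists and intervention implementers (clinical mentors) are aware of which cluster is receiving the intervention".

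The same therapists are close to the data:

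- *Randomisation* (enrollment): "During data collection periods, patients will be recruited by their physiotherapist", and the therapist also takes consent.
- The baseline questionnaire has the physiotherapist complete the functional scale with the patient and ask the questions that lead to the rating.
- *Settings and locations* gives the 12-month telephone follow-up to the participating physiotherapists.

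On timing, *Intervention* states: "The first step (time point) corresponds to a baseline measurement where none of the clusters receive the intervention". Each step lasts 12 months. Mentoring comes at the start and patient data collection towards the end.

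**The concern.** In a stepped wedge with one-way crossover, therapists cannot be blinded to their current status. They can be kept from knowing their future status, and the protocol does not do this. A therapist who knows that mentoring starts in a few weeks, or not for years, may change effort, approach patients for consent differently, set different PSFS activities or seek other training. Because data are collected at the end of a step and mentoring is given at the start of the next, a cluster's last control patients are treated just before its mentoring begins, when anticipation is most plausible. *Validity approaches in quantitative methods* itself lists demoralisation of control participants as a threat. Its answer is that everyone benefits eventually and receives usual training meanwhile. That does not cover what therapists do once they know the date.

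At stake is bias in the primary effect estimate, through the control observations that the model uses most.

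**Working it through.** **Inputs.** From *Power calculation: summary*, *Base case details* and Appendix E: 12 therapists; 4 steps; 3 clusters, one crossing at each of steps 2, 3 and 4; N = 9 patients per therapist per step; σ_e = 2; τ = 1. The target comes from the instruction to "assume that the average effect of the intervention is 1". With 4 therapists per cluster, each cluster-step cell holds 4 × 9 = 36 patients.

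**Step 1: reproduce the protocol's power.** With s² = 4/9, τ² = 1, U = 24, W = 224 and V = 56:

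Var = I·s²(s² + Tτ²) / [(IU − W)s² + (U² + ITU − TW − IV)τ²]
= (5.3333 × 4.4444) / (28.444 + 160) = 23.704 / 188.444 = 0.12579.

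Δ = 1/√0.12579 = 2.8196 and two-sided power is 0.805, as in Appendix E. (The summary prints Δ with the variance in the denominator, which would give 7.95. The spreadsheet uses the SD, so the stated power stands.)

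**Step 2: weight of each cell in the effect estimate.** The generalised least squares estimate is linear in the cell means. With V = s²I + τ²J for each therapist and Z_i holding the step indicators and treatment indicator, the weights are the treatment row of (ΣZ_i′V⁻¹Z_i)⁻¹Z_i′V⁻¹, summed over the four therapists in a cluster. At τ = 1, with clusters numbered by order of crossing (c = control, m = mentored):

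| Cluster | Step 1 | Step 2 | Step 3 | Step 4 |
|---|---|---|---|---|
| 1 | -0.255 c | +0.500 m | +0.123 m | -0.255 m |
| 2 | 0 c | -0.377 c | +0.377 m | 0 m |
| 3 | +0.255 c | -0.123 c | -0.500 c | +0.255 m |

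The three last-control cells sum to -1.132. Absolute control weight is 0.255 + 0.377 + 0.255 + 0.123 + 0.500 = 1.51, so these cells carry 1.132/1.51 = 75% of it. Of the total absolute weight of 3.019 they carry 37.5%. The first post-crossover cells (0.500 + 0.377 + 0.255 = 1.132) carry the same.

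**Step 3: effect of a shift b in the last-control cells.** The size of b is an assumption, because the documents give none.

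| τ² | Cluster 1, step 1 | Cluster 2, step 2 | Cluster 3, step 3 | All three | Clusters 1 and 2 only |
|---|---|---|---|---|---|
| 0 | 0 | -0.250 | -0.500 | -0.75b | -0.25b |
| 0.05 | -0.066 | -0.283 | -0.500 | -0.85b | -0.35b |
| 0.2 | -0.159 | -0.329 | -0.500 | -0.99b | -0.49b |
| 1 | -0.255 | -0.377 | -0.500 | -1.13b | -0.63b |
| 10,000 | -0.300 | -0.400 | -0.500 | -1.20b | -0.70b |

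At τ = 1, b = -0.1, -0.25 or -0.5 adds 0.11, 0.28 or 0.57 to the estimate.

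**Step 4: what withholding the order can remove.** Therapists know which cluster is being mentored. By step 3 two clusters have crossed, so the third knows its turn by elimination under any scheme, and its -0.500b remains. The avoidable part is -0.255b - 0.377b = -0.63b, or 0.06, 0.16 and 0.32 for the same three shifts. Anything cluster 3's knowledge does in steps 1 and 2 (weights +0.255 and -0.123) is also avoidable.

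In patients, there are 6 × 36 = 216 planned control observations: 108 in step 1, 72 in step 2 and 36 in step 3. With sealed, staged disclosure, 108 + 72 = 180 would be collected by therapists who do not know their crossover date. At present the text protects none of them.

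**The case against.** The strongest reply is that key facts are inferred. No passage dates the draw relative to step 1, and none says therapists are told the future order; *Blinding (Masking)* speaks of the cluster currently receiving mentoring. That is right. A reader might infer that the protocol orders early disclosure, but it does not: it leaves disclosure open. An early draw is also not itself an error, since 150 hours of mentoring from in-service staff need planning. What stands is that the protocol sets out whom it conceals the order from and leaves out those who recruit patients and help complete the PSFS.

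Second, the size and sign of any shift are assumed. A reader might infer that the effect will be overstated, but extra self-training before crossover would understate it. Lower gains in cluster 3 at step 1 would also pull the estimate down, because that cell's weight is positive. A shift common to all control cells passes through as exactly -1.0b.

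Third, a reader might infer that the estimate rests mainly on pre-crossover patients. That is true only among control cells, since the first post-crossover cells weigh the same. The shift passes through more than one-for-one at the base case but not at small τ.

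Fourth, there are safeguards: consecutive recruitment, patients unaware of therapist status, risk adjustment, specified control training with non-receipt reported, and a rating that the patient gives. These reduce the scope for bias. They do not control therapist effort, how consent is sought or which PSFS activities are chosen.

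Last, timing limits any remedy. Patients are collected at the end of each step, so announcing the next cluster before that step ends would fall in the recruitment window. If it overlapped step 2 collection, clusters 2 and 3 would both learn their turn, and (0.377 + 0.500)|b| would remain. This objection stands, and disclosure has to follow the close of collection.

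**Conclusion.** The concern holds as a concealment gap that should be closed. It is not a demonstrated bias. The protocol fixes the full order in one draw after therapist consent and does not withhold it from the therapists who recruit control patients, complete the PSFS with them and make the follow-up calls. At τ = 1 an assumed shift b in the last control steps moves the estimate by -1.13b (-0.75b at τ = 0, about -1.2b at large τ), of which about -0.63b (-0.25b to -0.7b) could be avoided. For shifts of -0.1 to -0.5 the total is about 0.11 to 0.57 of the 1-point target and the avoidable part about 0.06 to 0.32. These figures rest on the protocol's model, equal cell sizes and an assumed shift confined to the last control steps; other patterns could bias the other way.

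One limit applies to the 12-month data. Patients collected at the end of a step are called about a year after discharge, by which time that cluster's next step has largely passed. Therapists calling their last control patients will usually have crossed over by then, and withholding the order does not mask those calls.

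**What to change.** 1. State under *Randomisation* and *Blinding (Masking)* that the order is withheld from participating therapists as well as from the lead researcher. The mentors may hold it for rota planning, on condition that they do not pass it on.
2. Disclose only the next cluster, and only after the current step's patient recruitment and discharge PSFS collection have closed. Take the notice period from the start of the next 12-month step.
3. Keep the remaining order sealed until the same point in the following step.
4. Acknowledge that the last cluster can deduce its turn once the second has crossed.

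The cost is protocol wording, shorter notice for therapists' clinic rotas and slightly less consolidation time within the step. No design input changes: the variance stays at 0.1258, power at 0.805 and the planned total at 4 × 12 × 9 = 432 observations.
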